**Figure 1 figure1:**
[figure not shown]
Home page interface of the gamified pain management intervention.

**Figure 2 figure2:**
[figure not shown]
Choice feature interface.

**Figure 3 figure3:**
[figure not shown]
Room background and points feature interface.

**Figure 4 figure4:**
[figure not shown]
Quiz function interface.

### Control Group

In the control group, participants will receive a digital pain management resource package for a 10-week period, containing the same components as the gamified pain management group but delivered in a nongamified, standard digital format. The package contains educational content, exercise videos, educational videos, and relaxation audios that are identical in content and volume to those used in the gamified pain management group, delivered via an online PDF handbook with hyperlinks through WeChat. These multimedia resources are hosted on WeChat and the Xiaohongshu official account to ensure accessibility. In addition, participants will receive interim reminders biweekly via WeChat, encouraging them to read the handbook and engage in exercises, relaxation, and educational activities to promote adherence throughout the intervention period.

### Outcome Measures

The T0 (baseline before intervention), T1 (immediately after intervention), and T2 (the 3-month follow-up) assessments will be collected via the Wenjuanxing platform [39].

#### Primary Outcome

Pain intensity and pain interference are assessed using the Brief Pain Inventory between baseline, T1, and T2, rated from 0 (no pain) to 10 (worst pain). Pain severity is calculated based on pain experienced in the past 24 hours and “current pain.” Pain interference includes the degree to which pain interferes with general activity, mood, walking, work, social relationships, sleep, and enjoyment of life. The Chinese version has good reliability, with Cronbach α=0.89 [51].

#### Secondary Outcomes

##### Study Instruments

The Fear Avoidance Beliefs Questionnaire is used to measure fear of pain and consequent avoidant behaviors related to physical activity. The questionnaire consists of 16 items; each rated on a 7-point Likert scale ranging from 0 (completely disagree) to 6 (completely agree). The Cronbach α of the Chinese version ranges from 0.75 to 0.85 [52].

The Pain Catastrophizing Scale is used to measure pain catastrophizing beliefs, including 3 subscales, rumination, magnification, and helplessness, rated from 0 to 4. Higher scores indicate stronger pain catastrophizing beliefs. The Cronbach α of the Chinese version is 0.91 [53].

The Godin-Shephard leisure-time physical activity questionnaire is used to measure exercise adherence, including frequency of strenuous, moderate, and mild exercise per week. The percentage of exercises completed out of the total number of prescribed exercises is used to measure total exercise adherence [54].

The Patient Health Questionnaire-9 is used to assess the symptoms of depression, scored on a 4-point Likert scale from 0 (not at all) to 3 (nearly every day). Higher scores indicate greater severity of depressive symptoms. The Cronbach α of the Chinese version of this questionnaire is 0.86 [55].

The Generalized Anxiety Disorder-7 is used to measure anxiety, including 7 items rated from 0 (not at all) to 3 (nearly every day). The Chinese version has excellent internal reliability, with a Cronbach α of 0.91 [56].

The 3-level version of the EuroQol-5D is used to assess an individual’s perceptions of quality of life, including mobility, self-care, usual activities, pain and discomfort, and anxiety and depression. Each dimension is evaluated with 3 levels of severity. Higher scores indicate a lower level of quality of life. The Chinese version has been treated as the standard in China [57].

The Game User Experience Satisfaction Scale-18, an 18-item scale is used to evaluate overall user satisfaction with the game, rated from 0 (strongly disagree) to 7 (strongly agree), with good internal reliability (Cronbach α=0.93) [58]. Higher scores indicate a higher level of satisfaction.

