**Methods:**

A 2-arm, single-blind randomized controlled trial will recruit 172 participants through Chinese hospitals and online platforms. Eligible participants will be randomized to 2 groups: a 10-week gamified pain management program for the experimental group and routine online pain management materials for the control group. Primary outcomes, including pain intensity and pain interference, and secondary outcomes, including fear avoidance, emotion, exercise adherence, quality of life, and user satisfaction, will be assessed at baseline, after the intervention (10 weeks), and at a 3-month follow-up. A mixed-design ANOVA and intention-to-treat analysis will be used to evaluate intervention effects.

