To address this gap in the literature, an online gamified pain management program, based on an escape room task, will be developed and augmented with game elements. The aim of this study is to investigate the effects of online gamified pain management in a sample of adults with chronic noncancer pain via a randomized controlled trial. To this end, the objectives will be to (1) examine the effects of the gamified pain management intervention on the levels of pain intensity, pain interference, psychological outcomes, and quality of life among adults; (2) assess exercise adherence and game experience in the gamified home-based management program; and (3) identify the relationships between the effects of the intervention and sociodemographic factors.

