### Study Intervention

The design of the gamified pain management is based on established gamification principles and frameworks [44,45] and is theoretically grounded in self-determination theory (SDT), which supports individual autonomy, competence, and relatedness to improve intrinsic motivation and sustain engagement [46]. The intervention was co-designed by an expert in chronic pain ([name]) and an expert in digital health ([name]), with contributions from the lead researcher (JH), a pain clinic clinician, a physiotherapist with more than 5 years of experience, and 3 internet technology specialists. The intervention is delivered via the web-based platform VxEditor [47], which is accessible on both smartphones and computers, over a maximum of 10-week period, allowing participants to complete the program at their own pace. In addition, participants can choose their specific pain site via the platform, which tailors exercises accordingly and thus improve autonomy.

The gamified pain management is designed as an “escape room” game. Participants assume the role of a hero (avatar) guiding others to escape from a metaphorical “pain room,” which fosters a sense of relatedness. The intervention consists of 8 core “rooms” (sessions). Participants must complete various challenges, including unlocking 10 clues and accumulating at least 60 points to progress from one session to the next, which is designed to foster a sense of competence. Participants are awarded 5 points for completing each exercise task and 2 points for correct quiz answers, while skipping an exercise earns no points. To further support competence and reinforce the knowledge of pain, immediate and automatic feedback is provided, offering affirmation and encouragement for correct quiz answers and explanatory feedback for incorrect answers. Four optional hidden sessions are also available, offering additional challenges for highly engaged users. A detailed overview of the gamification design is provided in Table 1.

**Table 1 table1:** Gamification design of the interventions.

Game elements	Applicable gamified interventions
Anonymity	Users are anonymized and represented by a unique code.
Avatar	Users assume the role of a hero (avatar) in the game.
Narrative	A background story (escape from the pain room) is presented to engage users.
Tutorials	Introductory tutorials establish an emotional connection with users and provide step-by-step instructions.

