Choices	Users can select different games based on their specific pain site.
Feedback	Users receive notifications upon completion of exercises and correct quiz answers.
Points	Users earn points for completing exercises and quizzes and for progressing to the next sessions.
Progression and leaderboard	A progress number indicates the level of effort achieved.
Challenges and rewards	Completing challenges unlocks hidden games with additional exercise opportunities.

The contents of the intervention consist of exercises complemented with education and relaxation practices, which are identified as “clues” within each session. Education topics are presented through animated videos and written notes, focusing on pain mechanisms, neurobiology and neurophysiology, the biopsychosocial model of pain, and management strategies [48]. Quizzes are used to assess and reinforce knowledge from the educational content. A total of 28 prerecorded exercise videos demonstrate stretching, strengthening, balance, and resistance exercises [49], tailored to specific pain areas (eg, neck, shoulder, back, knee, or head). The program recommends at least 60 minutes of exercise per week, and the completion of each exercise is verified via an in-video dialogue prompt that appears midway through the video, which participants must click to earn points. The relaxation practices are presented through recorded audios that guide participants in breathing exercises and muscle relaxation [50]. In addition, participants are required to solve real-world case puzzles by applying their knowledge to determine the mechanisms of chronic pain, which is a key task for session completion. Details of these components are shown in Table 2.

**Table 2 table2:** The gamified pain management intervention components.

Session	Clue components
1	Exercise: three 6-minute balancing exercises Educational information: pain mechanisms Relaxation audio: breathing exercises Quiz and puzzle
2	Exercise: three 6-minute stretching exercises for different pain sites Educational information: etiology of pain Relaxation audio: breathing exercises Quiz and puzzle
3	Exercise: three 6-minute core strengthening exercises Educational information: neurobiology and neurophysiology of pain Relaxation audio: muscle relaxation Quiz and puzzle
4	Exercise: three 6-minute stretching exercises for different pain sites Educational information: biopsychosocial model of chronic pain Relaxation audio: muscle relaxation Quiz and puzzle

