5	Exercise: three 6-minute core strengthening exercises Educational information: attention system and pain and distraction from pain Relaxation audio: body scan Quiz and puzzle
6	Exercise: three 6-minute balancing exercises for different pain sites Educational information: medication use and drug abuse Relaxation audio: body scan Quiz and puzzle
7	Exercise: three 6-minute core strengthening exercises Educational information: physical activity for chronic pain Relaxation audio: relaxation music Quiz and puzzle
8	Exercise: three 6-minute resistance exercises Educational information: nonpharmacological strategies Relaxation audio: outdoor relaxation Quiz
Four hidden sessions	Exercise: three 20-minute stretching and resistance exercises

The gamified pain management platform automatically captures and stores detailed engagement data on a secure, cloud-based back end. The latest room successfully completed is recorded, allowing research staff to track progress. Time stamps for the first log-in and last interaction with the platform are also generated to calculate the total time spent. Quiz accuracy rates and total points accumulated are stored on the backend, enabling monitoring by the research team. To promote adherence, interim reminders will be sent via WeChat biweekly to participants who have not progressed at the expected pace. After completing the program, participants are encouraged to continue using the platform for practice. Screenshots of the gamified pain management are provided in Figures 1-4.

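### Two different constructs are called exercise adherence; the one clearly available in both arms is a general activity questionnaire with no link to the programme

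*Protocol article*

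**What the plan says.** In the Study Instruments section, under Secondary Outcomes, two consecutive sentences define adherence. The first reads: "The Godin-Shephard leisure-time physical activity questionnaire is used to measure exercise adherence, including frequency of strenuous, moderate, and mild exercise per week". The second reads: "The percentage of exercises completed out of the total number of prescribed exercises is used to measure total exercise adherence". The article does not say which of the two is the adherence outcome.

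Adherence appears in three other places:
- The second objective, at the end of the Introduction, is to "assess exercise adherence and game experience in the gamified home-based management program".
- The Methods paragraph of the Abstract says that "secondary outcomes, including fear avoidance, emotion, exercise adherence, quality of life, and user satisfaction, will be assessed at baseline", and then at the two later visits.
- Anticipated Findings expects adherence to be higher in the gamified arm than in the control arm.

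On data capture, Study Intervention says that an exercise counts as done when the participant clicks a prompt shown partway through the video, and that engagement data are stored by the platform. Control Group describes the same content supplied as a PDF handbook with links, and gives no way of recording which exercises were done.

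**The concern.** Adherence is what was done relative to what was prescribed. The questionnaire, as the article describes it, asks how often a person does strenuous, moderate and mild exercise in a week. It has no prescribed reference and does not separate programme exercise from any other. The exclusion criteria bar supervised exercise programmes and multidisciplinary treatment, so a participant's own walking, sport or gym use is allowed and counts.

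The percentage completed is a measure of adherence, but its capture is described in one arm only. The adherence hypothesis compares the arms. If it is tested with the measure that both arms clearly have, a difference in general activity would be reported as a difference in adherence to the programme. That would bear on the article's central argument, which is that gamification keeps people engaged with the same content.

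**Working it through.** The plan states no figure on this point, so there is none to reproduce. The check has two parts.

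**1. How a programme completer and a non-user score on each measure**

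Inputs:
- 8 core sessions (Study Intervention).
- 3 exercises of 6 minutes in each core session (Table 2, sessions 1 to 8).
- 4 optional hidden sessions. Table 2 gives "Exercise: three 20-minute stretching and resistance exercises", read here as three in each hidden session.
- Duration: "over a maximum of 10-week period, allowing participants to complete the program at their own pace". The full 10 weeks is used.
- A recommendation of at least 60 minutes of exercise a week (Study Intervention).

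Assumptions: each exercise counts as one occasion, occasions are not weighted by intensity, each video is done once, and the completer does no other exercise.

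Core programme:
- Exercises: 8 × 3 = 24, or 24 / 10 = 2.4 a week.
- Time: 24 × 6 = 144 minutes, or 14.4 minutes a week.

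Core plus all hidden sessions:
- Exercises: 24 + 4 × 3 = 36, or 36 / 10 = 3.6 a week.
- Time: 144 + 12 × 20 = 384 minutes, or 38.4 minutes a week.

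Now take a person who does none of the programme and exercises elsewhere *f* times a week:

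| *f* per week | Above core completer (2.4)? | Above core + hidden completer (3.6)? | Percentage completed, non-user against completer |
|---|---|---|---|
| 2 | no | no | 0% against 100% |
| 3 | yes | no | 0% against 100% |
| 4 | yes | yes | 0% against 100% |

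On weekly frequency the order reverses from 3 or 4 outside sessions a week. On the percentage it cannot reverse at any *f*.

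The thresholds depend on the assumptions:
- A single pass through the videos (14.4 or 38.4 minutes a week) falls short of the recommended 60 minutes. Reaching it with six-minute videos takes 60 / 6 = 10 exercises a week, and the non-user would then need more than 10 sessions to rank higher.
- Finishing the core sessions sooner also raises the weekly count while it lasts. For example, 24 exercises in 6 weeks is 24 / 6 = 4.0 a week.
- If the hidden-session row means three exercises in total, the single-pass total is 24 + 3 = 27, or 2.7 a week, and the threshold is 3.

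**2. Which measure exists in which arm**

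| Measure | Gamified arm | Control arm |
|---|---|---|
| Questionnaire | survey platform, T0, T1, T2 | survey platform, T0, T1, T2 |
| Percentage of prescribed exercises completed | click within the video, platform data | no capture described |

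On the text shown, only the questionnaire is clearly available for a comparison between arms.

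**The case against.** The strongest reply is that the article already contains the right measure. A reader might infer from the first sentence alone that adherence is scored by the questionnaire, so that a non-user is ranked as the more adherent. The document does not support that, because the very next sentence defines total adherence as the percentage completed, and the reversal is impossible there. This stands, and it limits the point to the questionnaire.

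Three further replies also have force:
- The programme sets a weekly exercise target, so a weekly-frequency questionnaire is a plausible, if imperfect, proxy. A single-pass completer does not reach that target, so calling that person fully adherent can be disputed.
- The planned analysis compares randomised arms over T0, T1 and T2 and does not rank individuals. Stable outside activity is balanced in expectation and drops out of the group-by-time contrast. It adds noise but does not by itself create an arm difference.
- The Abstract's listing of adherence at baseline is weak evidence of error, because the same list includes user satisfaction, which also cannot exist before the game is used. It reads as loose condensation.

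None of these removes the naming problem. A real arm difference in leisure activity, on or off the programme, would still carry the label of adherence. Nor is this detail merely left to another document: the article itself assigns the name to the instrument.

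**Conclusion.** The point holds in a limited form. One name covers two constructs, and the questionnaire is not tied to the programme. With each video done once over 10 weeks and no other activity, a completer contributes 2.4 to 3.6 occasions a week, which 3 to 4 outside sessions exceed. Repetition or a faster pace raises that threshold, so these figures illustrate the mismatch and are not a ceiling on what the programme adds.

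A reader might also want to state what share of participants would be ranked the wrong way. The document gives neither usual activity levels nor expected completion, so no such share can be derived from it.

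That the between-arm hypothesis would rest on the questionnaire is probable, not certain. It depends on completion not being recorded in controls, and the article describes no such recording. The point concerns a secondary outcome and its interpretation; the primary pain outcomes are unaffected.

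**What to change.** - In Study Instruments, the Methods paragraph of the Abstract and Anticipated Findings, call the Godin-Shephard result *leisure-time physical activity*. Compare it between arms with its T0 value taken into account, and draw no adherence conclusion from it.
- Keep *exercise adherence* for the percentage of prescribed exercises completed.
- For that percentage, do one of two things. Either state how it is obtained in the control arm, or report it descriptively in the gamified arm only and restate the hypothesis in Anticipated Findings to match.

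The Study Timeline section says that data analysis has not started, so the names can be settled before any results are seen. Relabelling is a wording change. Obtaining completion in controls would need a means of capture that the article does not now describe. Without it, the trial gives up a between-arm claim about adherence, although it can still compare leisure-time activity between the arms.

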##### Intraintervention Variables (Collected During or Immediately After the Intervention)

Engagement metrics are assessed through session-specific satisfaction scores (Satisfaction scores for sessions 1 to 8) and quiz accuracy, recorded via the gamified pain management platform. Satisfaction scores are derived from the sum of 3 items rated on a 5-point Likert scale following the completion of each session. These items evaluate the following: (1) understandability (“Are the materials in this session easy for you to understand?”), (2) comprehensibility (“How much do you understand the materials in this session?”), and (3) applicability (“To what extent do you think you would apply this session to future self-management?”). Quiz accuracy is calculated as the proportion of correctly answered questions in each session’s embedded quiz.

Treatment duration is automatically calculated as the total number of weeks between a participant’s first and last log-in on the gamified pain management platform.

##### Semistructured Interviews

Semistructured interviews are conducted by JH after completion of the intervention to measure participants’ perceptions, attitudes, and experiences after participating in the intervention. Interviews will be conducted via a private online Tencent Meeting room (version 3.37.10.401; Tencent Meeting) [59], ensuring that participants’ confidentiality and privacy are protected. In addition, perceived motivators and barriers related to gamification elements will be explored. Each interview will last 40 to 60 minutes. Examples of semistructured interview questions are provided in Textbox 1.

Examples of interview questions.How has your pain intensity changed since the start of the gamified pain management intervention?What changes have occurred in your perception of pain since you started receiving the gamified pain management intervention?What aspects of gamified pain management do you think are most beneficial? How about the game elements?What challenges or difficulties have you encountered when using the gamified pain management intervention?Which game element do you find most useful, and why?Do you plan to continue using the GPM intervention after this study? If not, what barriers are preventing you from continuing?What suggestions do you have for improving the gamified pain management intervention?

### Statistical Analysis

SPSS (version 25.0; IBM Inc) will be used for all statistical analyses. An intention-to-treat analysis will be used, whereby all participants will be analyzed in the context of the groups to which they had been originally assigned. Descriptive statistics for feasibility will include the following: (1) the percentage of participants recruited from the total number approached; (2) the percentage of participants (among those recruited) who are retained in the study at the end of 3 months in each arm and overall; and (3) engagement metrics, including completion status, duration of the intervention, and rate of accuracy on quizzes.

To detect potential differences in sociodemographic and baseline clinical characteristics, the *χ*^2^ test with continuity correction (or the 2-sided Fisher exact test when appropriate) will be used for categorical variables, and the *t* test will be used for continuous variables. The normality of distributions will be confirmed using the Shapiro-Wilk test before statistical analysis. Repeated measures ANOVA (mixed design: within and between groups) will be used to determine the overall effectiveness of the intervention. Missing values will be addressed using intention-to-treat principles with maximum likelihood estimation, assuming data are missing at random. Statistical significance will be set at *P*<.05.

The interviews will be transcribed verbatim and reviewed. Open and axial coding will be used for data identification and integration, resulting in different meaning categories derived using grounded theory methods. NVivo (QSR International Inc) will be used for the coding process and information handling.

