## Methods

### Study Design and Setting

This study is a 2-arm, single-blind (analysts are blinded), randomized controlled trial. A total of 172 individuals with chronic pain will be recruited and randomly assigned to either gamified pain management program (intervention group) or a digital resource package (control group). The interventions for both groups will be delivered online. Participants will complete outcome assessments at 3 time points: baseline (T0), immediately after the intervention (T1), and at a 3-month follow-up (T2). This study protocol follows the SPIRIT (Standard Protocol Items: Recommendations for Interventional Trials) guidelines [23].

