### Sample Size

A previous power analysis was used for sample size calculations using G*Power software (version 3.1; Heinrich-Heine-Universität Düsseldorf) [24]. To establish the effect size for the sample size calculation, we synthesized evidence from multiple sources. A meta-analysis analyzing the effects of serious games on pain intensity in patients with chronic pain reported a mean difference of −0.62 (95% CI −1.15 to −0.10) for pain reduction [18]. To supplement this, we conducted another meta-analysis of 12 relevant studies examining the effects of gamification on pain intensity in adults. The results yielded a mean difference of −0.86 (95% CI −1.61 to −0.11) [25-36]. However, given that our digital intervention comprises mixed physical, psychological, and educational components, we also incorporated evidence from 2 other meta-analyses including online pain management and multidisciplinary programs, with effect size of −0.30 (95% CI −0.50 to −0.10) [12] and −0.57 (95% CI −0.63 to −0.50) [37].

Therefore, to ensure robust and conservative statistical power, we selected a medium effect size of 0.50 to reduce potential bias or heterogeneity [38]. The following parameters were used: power (1−β)=0.90, effect size=0.50, and α=.05 (2 tailed). Taking a 20% margin for dropout and missing data, a total of 172 participants will be recruited, with 86 allocated to the experimental group and 86 to the control group.

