### Anticipated Findings

We hypothesize that participants in the gamified pain management intervention will report a substantial reduction in pain intensity and pain interference compared with the control group at both postintervention and 3-month follow-up. Furthermore, the gamified pain management group is expected to exhibit greater improvements in secondary outcomes, including emotional distress, fear-avoidance beliefs, and pain catastrophizing, as well as higher engagement and exercise adherence. In addition, recovery is expected to be associated with sex, age, and socioeconomic status.

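### The trial expects a benefit over control at both follow-up visits, but the omnibus mixed ANOVA that judges effectiveness does not show the arm difference at either visit

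*Protocol article*

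**What the plan says.** Outcomes are collected at "baseline (T0), immediately after the intervention (T1), and at a 3-month follow-up (T2"). On the primary outcomes, the Primary Outcome section states: "Pain intensity and pain interference are assessed using the Brief Pain Inventory between baseline, T1, and T2".

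The Anticipated Findings section expects a greater reduction in both "compared with the control group at both postintervention and 3-month follow-up".

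The Statistical Analysis section assigns the decision as follows: "Repeated measures ANOVA (mixed design: within and between groups) will be used to determine the overall effectiveness of the intervention". The abstract agrees: "A mixed-design ANOVA and intention-to-treat analysis will be used to evaluate intervention effects". Neither place names an F term or a between-arm comparison at a given visit. The Statistical Analysis section also commits to maximum likelihood estimation for missing values, assuming they are missing at random.

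The Sample Size section uses "power (1−β)=0.90, effect size=0.50, and α=.05 (2 tailed"). It then states: "Taking a 20% margin for dropout and missing data, a total of 172 participants will be recruited".

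**The concern.** The scientific claim concerns two separate quantities, the arm difference at T1 and the arm difference at T2. The stated decision tool is an omnibus analysis that yields three F tests, none of which isolates either quantity. A significant result therefore does not tell the reader whether the advantage over control was still there at 3 months, and durability is half of what the trial expects to show.

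The comparator makes this matter more. The control package is described as "identical in content and volume to those used in the gamified pain management group", so gamification is the main contrast between the arms. Whether any added benefit outlasts the 10-week programme is a central question.

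**Working it through.** **Inputs from the article.** 86 per arm, visits T0, T1 and T2, effect size 0.50, two-sided alpha .05, 20% margin for loss.

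**Assumed, because the article gives no figures.** SD 1 at each visit, equal correlation ρ between visits of 0.3, 0.5 or 0.7, complete data, and equal arm means at baseline (randomisation).

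**1. The plan's own figure.** A two-sample t test with d = 0.50, two-sided alpha .05 and 86 per arm has power 0.903. The sample size thus matches one between-arm comparison at one time, before any loss. With 20% loss, 86 × 0.8 = 68.8, about 69 per arm, and power is about 0.83. (Whether 172 really contains the margin is a separate matter.)

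**2. What each F test tests.** Write δ0, δ1, δ2 for the arm differences at T0, T1, T2.
- Time: no change over visits with the arms pooled. Allocation plays no part.
- Group: δ0 + δ1 + δ2 = 0, baseline included.
- Group by time (2 df): δ0 = δ1 = δ2. With δ0 = 0 this means δ1 = 0 and δ2 = 0 together, so one non-zero visit is enough to make it false.
- The expectation of benefit at both visits fails if δ1 = 0 or δ2 = 0. None of the three has that null.

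**3. Interaction.** The noncentrality is λ = (n/2) × Σ(δk − mean δ)² / (1 − ρ), on 2 and 2(2n − 2) = 340 df.
- Effect at T1 only, (0, 0.5, 0): mean 1/6, sum of squares 1/36 + 4/36 + 1/36 = 1/6.
- Effect at both, (0, 0.5, 0.5): mean 1/3, sum of squares 4/36 + 1/36 + 1/36 = 1/6.

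The two are equal. In either case λ = 43 × (1/6) / (1 − ρ) = 7.167 / (1 − ρ), which is 10.24, 14.33 and 23.89 for ρ = 0.3, 0.5 and 0.7. The noncentral F gives rejection in 82%, 93% and 99.5% of trials. Simulation (6,000 runs per cell) agrees: 82%, 93% and 99.5% for T1 only, and 82%, 93% and 99% for both. The omnibus interaction cannot distinguish a vanished effect from a lasting one. With 69 per arm the figures are 72%, 86% and 98%.

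**4. Group term, effect 0.5 SD at both visits.** The tested difference shrinks to (0 + 0.5 + 0.5)/3 = 0.333. Its standard error is √[(2/n)(1 + 2ρ)/3] = 0.111, 0.125 and 0.136. The ratios are 2.99, 2.68 and 2.44, giving power of 85%, 76% and 68%.

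**5. Baseline-adjusted contrasts at T1 and T2**, each at two-sided .05 and in favour of the intervention (simulated):

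| Scenario | n per arm | ρ = 0.3 | ρ = 0.5 | ρ = 0.7 |
|---|---|---|---|---|
| Effect at T1 only: both significant | 86 | 2.5% | 2.6% | 2.3% |
| Effect at both: both significant | 86 | 87% | 93% | 99% |
| Effect at both: both significant | 69 | 75.5% | 86% | 96.5% |

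**6. Equal improvement of 0.3 SD in both arms, no gamification effect (86 per arm).** The time F rejects in 94%, 99% and 99.9% of trials. The group and interaction tests each stay near 5%.

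**The case against.** Four counter-arguments deserve weight.

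- A journal article commonly leaves follow-up contrasts to a fuller plan, which is not shown. This stands as far as it goes: a missing contrast alone would be no finding. A reader might infer that the 3-month effect is never tested, but nothing in the article rules out visit contrasts elsewhere. What remains is that the article itself states a two-visit expectation and assigns the verdict to an omnibus test that cannot answer it.
- If there is a real effect at T1, rejecting the interaction null is correct. This also stands. The 82% to 99.5% is not a false-positive rate of the F test. It is the rate at which the test would be significant when there is no benefit at T2, so the error arises only if that result is read as sustained benefit.
- Benefit at both visits appears as an expectation, not as a success rule. This is right, and the remedy should not turn it into a condition for trial success.
- If the interaction is the intended term, its power for an effect at both visits is 82% to 99.5%, so the visit contrasts gain little there. True: the clear power shortfall is in the group term. The gain over the interaction is in interpretation.

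A stronger reading is tempting: that the trial could declare gamification effective because both arms improved over time. The article does not support it. No sentence makes the time effect the test of effectiveness, the bracketed mention of within and between groups most naturally names the design factors, and the hypothesis is worded against control. In that scenario the group and interaction tests hold their level near 5%.

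**Conclusion.** The concern holds in a limited form: the stated omnibus test does not match the stated two-visit expectation. Under the usual interaction reading, a significant result is equally likely whether a 0.5 SD effect lasts to T2 or has gone by then (about 82% to 99.5%, 86 per arm). Under the group reading, baseline dilution leaves about 68% to 85% power for an effect present at both visits. These figures rest on complete data, equal variances and equal correlations of 0.3 to 0.7, none of which the article gives. That the two effect patterns have the same noncentrality does not depend on the value of the correlation. This is a low-cost improvement to how the primary conclusion is drawn. It does not show that the plan prescribes a wrong decision rule.

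**What to change.** Replace the effectiveness sentence in Statistical Analysis with wording such as: *Effectiveness will be judged from the baseline-adjusted between-arm differences at T1 and at T2, with 95% confidence intervals, estimated from a maximum-likelihood longitudinal model. A benefit will be claimed only at a visit whose own contrast supports it, and benefit at both time points only if both contrasts do. The time main effect and within-arm changes are descriptive.* The last sentence closes off a possible misreading and does not correct a stated rule.

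Baseline adjustment should be explicit. Without it, the chance of supporting the joint claim for a 0.5 SD effect at both visits was 83% to 84% with 86 per arm and 71% to 76% with 69, against 87% to 99% and about 76% to 96% with it.

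The cost is a wording change and a few lines of syntax. The maximum-likelihood estimation already promised points to the model needed, and no new data are required. The Study Timeline section reports 19 participants recruited by November 17, 2025 and analysis not yet started, so the change can still be prespecified. There are three downsides:
- An effect at T1 only cannot be reported as sustained.
- The chance of supporting the joint claim can fall below the planned 90%, as the figures above show.
- If single-visit claims are allowed at .05 each, the chance of at least one false claim per outcome can reach at most 0.05 + 0.05 = 10%, and the plan should say whether that is accepted. The joint claim needs no such allowance.
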